##### Measures

The framework identified in Fig. 1 has informed the battery of measures. Assessments will focus on organizational-, provider-, and patient-level domains (see Table 3). Primary outcomes will be feasibility and acceptability of the CCI and assessment procedures to be used in a larger trial [35]. Organizational outcomes will include pre- and post-intervention assessments of each clinic to gather data on organizational structure and procedures for care coordination. Provider outcomes will include feedback on the intervention component in Phase 1 and 2 of the trial; satisfaction of care coordination, frequency and quality of interagency communications, and interagency professional relationships; and potential moderators (e.g., stigma, perceived coercion). Patient outcomes will include demographics, viral load, and retention in dual care. Quantitative measures will be collected via web-based surveys from clinic leadership (n = 8) and providers (n = 60) at baseline and 1-, 3-, and 6-months post implementation of the CCI (Phase 3).

**Table 3 Tab3:** Outcome variables and assessment points

Quantitative measures	BL	Post-T	1-, 3- mos	6 mos	Analysis
Provider-level outcomes					
Provider descriptive information					
Provider demographics	X				Descriptive
Training in HIV and SU issues	X		X	X	Descriptive
HIV/SU treatment experience	X		X	X	Descriptive
Knowledge related to SU/HIV	X	X		X	Descriptive
Coercion assessment scale	X		X	X	Exploratory: Moderator
Provider perception inventory	X		X	X	Exploratory: Moderator
Provider acceptability and usability of the CCI and training protocol					
Satisfaction with training		X			Acceptability
CCI program satisfaction				X	Acceptability
Perceived attributes scale	X		X	X	Exploratory: Mediator
Interagency collaboration and communication					
Levels of collaboration scale*	X		X	X	Quant: Hyp 2
Frequency/quantity of communication*	MDE		MDE	MDE	Quant: Hyp 2
Wilder collaboration factors inventory	X			X	Exploratory: Moderator
Relational coordination					
Relational coordination scale*	X		X	X	Quant: Hyp 3
Organizational-level outcomes					
Organizational descriptives	X			X	Descriptive
Organization readiness	X		X	X	Exploratory: Mediator
Implementation climate scale	X		X	X	Exploratory: Mediator
Patient-level outcomes					
Descriptive information					
Demographics	MDE				Descriptive
Viral load	MDE			MDE	Descriptive
Dual care treatment retention	C/MDE			C/MDE	Quant: Hyp1

*BL* baseline, *I* implementation, *T* training, *MDE* Data extracted through the mobile app dashboard, *CDE* data extracted through clinic medical records, *EXPL* exploratory, *QUANT* quantitative, *HYP* hypothesis

* Primary Outcome Variable

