#### Hypotheses testing

Given the developmental nature of this study, our primary objective is to establish feasibility and acceptability of the CCI and assessment procedures. The following deliverables will result from this study: evidence-based training model adapted to HIV and substance use providers, mobile application tool for providers targeting care coordination, interagency communication protocol, and a training strategy for the CCI. This study will yield necessary data regarding the acceptability and feasibility of the approach to be implemented in a future larger scale multisite trial [35]. We are well aware of the dangers of relying exclusively on small-scale pilot studies to gauge the promise of a novel intervention [43]. Thus, we primarily will be hoping to find a pattern of results that is supportive of the CCI rather than rigorously testing hypotheses to determine a stable effect size. Hypotheses include: (1) Compared to baseline, providers will demonstrate increased dual care treatment retention as measured by data in the EHR; (2) Compared to baseline, HIV providers will report increased frequency and quantity of communication with substance use providers, and substance use providers will report increased frequency and quantity of communication with HIV providers; and (3) Providers will report improvements in relational coordination as measured by increased scores on the Relational Coordination scale between baseline and follow-up assessment. Group means on continuous variables typically begin to stabilize around 15 participants per group. For dichotomous variables, somewhat larger sample size is needed to provide reasonably stable odds ratios for effect size estimates. Therefore, the proposed sample size of 30 participants per group, even after attrition, will allow us to evaluate the potential of the CCI intervention to improve care coordination while remaining within the budgetary parameters for a preliminary trial.

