Tests of the effects of the intervention on the primary outcome variables (identified in Table 1 at BL, 1-, 3-, and 6-months) will be conducted using repeated measures ANOVAS on change scores. We will examine each organization separately and then develop a composite score to examine change across time. We will use repeated measures mixed model analysis of variance (ANOVA) to assess main effects and between-group effects on the primary and secondary dependent variables. We will test for the normality of the distributions, homogeneity of covariance matrices, and sphericity. If violations of the sphericity assumptions are found, we will use the Greenhouse Geyser Epsilon to adjust the probability of F [44]. Omnibus F testing will be followed by univariate tests to examine if primary outcome variables differ by condition (HIV vs SU provider). Analyses will be conducted using SAS Proc GLM, which allows for maximum use of observations across time even when some data are missing. To determine whether there was an effect of group, time, or a group × time interaction on the primary outcome variables specified a priori: (1) collaboration, and (2) frequency of interagency communication, and on the secondary outcome variable specified a priori: (1) interagency relationships as measured by relational coordination, we will conduct 4 repeated measures ANOVAs with 2 levels of condition (HIV provider and SU provider) and 3 levels of time (baseline, 3-mos FU, 6-mos FU). If the null hypothesis is rejected in omnibus testing, we will conduct further univariate tests of hypotheses for between-groups and main effects and calculate effect sizes for the effects observed across time (Eta squared). In addition, for each primary outcome variable at each follow up point, effect sizes and 95% confidence intervals will be computed.

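### Primary outcomes are labelled three different ways: relational coordination is both primary and secondary, four ANOVAs are planned for three named outcomes, and the label may decide whether an effect size is reported

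*Protocol article*

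**What the plan says.** Three places in the protocol article assign primary status.

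- **Measures, text.** "Primary outcomes will be feasibility and acceptability of the CCI and assessment procedures to be used in a larger trial". The Hypotheses testing section agrees at the level of aims: "our primary objective is to establish feasibility and acceptability of the CCI and assessment procedures".
- **Measures, Table 3.** The legend defines the asterisk as "Primary Outcome Variable". It is attached to the levels of collaboration scale, to frequency/quantity of communication, and to the row "Relational coordination scale". The two rows whose analysis is given as acceptability carry no asterisk.
- **Hypotheses testing.** Two primary variables are listed, collaboration and frequency of interagency communication. The tests are then extended to a third: "on the secondary outcome variable specified a priori: (1) interagency relationships as measured by relational coordination".

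The same sentence continues: "we will conduct 4 repeated measures ANOVAs with 2 levels of condition", with three levels of time (baseline, 3 and 6 months). The paragraph opens by referring to Table 1 for the primary outcomes.

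There are two routes to an effect size in that paragraph. The first is conditional: "If the null hypothesis is rejected in omnibus testing, we will conduct further univariate tests", together with eta squared for effects across time. The second has no significance condition, and gives effect sizes with 95% confidence intervals at each follow-up, but only for primary outcome variables.

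**The concern.** A reader cannot tell from the article which outcomes are primary. Relational coordination carries a formal label in two places, and the labels disagree. It is the subject of Hypothesis 3, so this is not a minor variable.

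The label also has a consequence. The Preliminary analyses section sets feasibility and effect-size estimation as the goal and expects few rejected null hypotheses. A rule that releases an effect size only after rejection works against that goal. Under the Hypotheses testing label, relational coordination is promised nothing more than the conditional route.

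Two things are at stake. One is room to give prominence, after the data are seen, to whichever outcome looks favourable. The other is that an estimate reported only because it was significant tends to be too large, and this pilot is meant to inform a larger multisite trial.

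**Working it through.** **1. Compare the labels.**

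| Outcome | Measures text | Table 3 | Hypotheses testing |
|---|---|---|---|
| Feasibility, acceptability | primary | not starred | primary objective |
| Collaboration | – | primary | primary |
| Communication | – | primary | primary |
| Relational coordination | – | primary | secondary |
| Dual care retention (Hypothesis 1) | – | no star; assigned to Hypothesis 1 | no rank |

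The Measures text shares no member with the other two lists. Table 3 and Hypotheses testing agree on two variables and conflict on one.

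**2. Count the ANOVAs.** Stated: 4. Named in that sentence: 2 primary + 1 secondary = 3. The stated figure is not reproduced. Possible sources of a fourth:

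- Dual care retention: the Abstract and Tables 1 and 3 place it at baseline and 6 months only, which gives 2 time levels, not the 3 in the model.
- Splitting communication into frequency and quantity: the sentence names frequency only, and Table 3 has one combined row.
- One model per starred row of Table 3: again 3.

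**3. Check the table reference.** Table 1 lists activities, timing and the provider, organizational and patient levels. It names no outcome variable. The asterisks are in Table 3.

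**4. Illustrate the freedom to choose.** The article states no alpha, so two-sided 0.05 is assumed. For k independent outcomes, the chance of at least one false positive is 1 − 0.95^k:

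- k = 2: 1 − 0.95² = 0.0975, or 9.8%
- k = 3: 1 − 0.95³ = 0.1426, or 14.3%

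These scales share raters and related constructs, so independence overstates the figures. With simulated equicorrelated normal statistics, as the correlation goes from 0.3 to 0.8, the chance falls from 9.5% to 7.9% for two outcomes and from 13.6% to 9.9% for three. One fixed outcome gives 5%.

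**5. Illustrate the gate.** Assumptions: n = 54 (90% of 60; the Missing data section cites follow-up above 90% in similar studies), alpha 0.05, and a one-sample t test on change as a simplification of the planned 2 × 3 ANOVA. With 53 degrees of freedom the critical t is about 2.006, so an observed standardized change must exceed 2.006/√54 = 0.273 to be reported. Simulation gives:

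| True change d | Share significant | Mean estimate if significant | Inflation |
|---|---|---|---|
| 0.2 | 30% | 0.36 | 1.8 |
| 0.3 | 58% | 0.40 | 1.3 |
| 0.4 | 82% | 0.45 | 1.1 |
| 0.5 | 95% | 0.52 | 1.04 |

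The inflation is serious for small true changes and negligible at 0.5.

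**The case against.** The best defence is that this is an uncontrolled pilot with modest aims. Feasibility and acceptability are its stated objective, so the Measures sentence can be read as the overall purpose and the starred rows as the quantitative variables that serve it. That reading is fair and softens the first disagreement. It leaves relational coordination with two opposite labels.

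A reader might infer that the outcome deciding the trial could be picked after the data are seen. The article does not support that. It states no alpha and no success rule, and the Discussion acknowledges the absence of a control condition, so no outcome decides anything. A reader might also take "we primarily will be hoping to find a pattern of results that is supportive of the CCI" as a declared intention to find a positive result. The sentence goes on to contrast this with rigorous hypothesis testing, and it follows a warning about relying on small pilots. Taken whole, it disclaims confirmatory use.

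The gate should not be overstated either. Collaboration and communication are primary in both Table 3 and Hypotheses testing, so their effect sizes are promised regardless of p. So is that of relational coordination if its asterisk stands. The gate affects one ranked outcome under one of two readings.

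Finally, dual care retention is not ignored: Table 3 assigns it to a quantitative test of Hypothesis 1. What it lacks is a rank.

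**Conclusion.** The point holds as an internal inconsistency. Relational coordination is formally primary in Table 3 and secondary in Hypotheses testing; the number of ANOVAs exceeds the outcomes named by one; the reference to Table 1 is wrong; and the outcome of Hypothesis 1 has no rank. None of this is detail that a condensed article leaves to a fuller document, because the article commits itself in each place.

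The consequence is selective emphasis and, for relational coordination under the secondary label, an estimate that might appear only when significant. The false-positive figures and the 1.04- to 1.8-fold inflation are illustrations. They rest on an assumed alpha of 0.05, assumed correlations, assumed true effects and a simplified test, and do not describe the planned ANOVA exactly. Severity: should be fixed.

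**What to change.** - Use one outcome hierarchy in the Measures text, Table 3 and Hypotheses testing. One workable form keeps feasibility and acceptability as primary and adds one fixed, ranked list of quantitative outcomes. Other rankings are possible if used consistently.
- Give relational coordination and dual care retention one label each.
- Change the reference for the primary outcomes from Table 1 to Table 3.
- Write 3 ANOVAs, or name the fourth outcome and confirm that it is measured at all three time points.
- Report effect sizes with 95% confidence intervals for every listed outcome, whatever the omnibus p value.

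The cost is a few edits to wording and one table, and slightly more reporting. No new data or change to the design is needed.

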### Present study

This study uses mixed methods to optimize care coordination of patients diagnosed with HIV and substance use issues using an organizational-level intervention that combines an evidence-based training approach with use of mobile technology. The proposed project consists of three phases. In Phase 1, we will use qualitative data to guide the development of the CCI and training approach. Phase 2 will consist of a series of functionality tests of the tablet-based mobile application prototype using fake patient data with HIV and SUD treatment providers, and a review of the intervention with a stakeholder panel of clinic leadership. Data regarding feasibility, acceptability, and barriers that would limit effectiveness of the intervention will guide modifications to finalize the software and the training protocol. In Phase 3, we will conduct a pre-, post-test trial of the CCI to examine its effects on the amount and quality of interagency communication, perception of interagency professional relationships, and retention of patients in dual care. Preliminary data regarding intervention costs and sustainability potential will be collected. Table 1 depicts the timing of key protocol elements for the Phase 3 pilot trial including provider enrollment, provider training, and assessments.

**Table 1 Tab1:** Timing of provider enrollment, training, and assessment activities

Timepoint	Enrollment	Training	Post-didactic training			
	-t1	0	Post training	+1 month	+3 months	+6 months
*Provider enrollment*						
Informed consent/assent	X					
*Training*						
Didactic sessions #1–3		X				
Interagency communication manual		X				
Internal change champions			X	X	X	X
External leadership coaching			X	X	X	X
*Assessments*						
Provider-level outcomes	X		X	X	X	X
Organizational-level outcomes	X			X	X	X
Patient-level outcomes	X					X

The primary goal of this protocol is to develop and test a CCI among HIV and SUD treatment providers. We hypothesize that the combination of training and mobile health tools specifically created for HIV and SUD care coordination will (a) increase patient retention in dual care, (b) increase the amount of communication between HIV and addiction treatment providers, and (c) improve relational coordination between HIV and SUD treatment providers.

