Interagency communication protocol	Include a manual for the mobile app and outline communication procedures and language
Didactic Session 1 (conduct separately at each clinic)	Provide study details, solicit buy-in and commitment to change, cross-training in HIV/SU issues
Didactic Session 2 (conduct concurrently at neutral location)	Train in CCI and study procedures, introduce participants from each clinic
Didactic Session 3 (conduct separately at each clinic)	Hands-on practice with the mobile application using fake patient data, pass a CCI competency test
Science to Service Laboratory (ATTC)	Appoint Internal Implementation Champions within each clinic; external leadership coach

Mobile application features				
Enable rapid communication	Patient linkage to dual care	Care coordination	Work flow	Dual care resources
Portable platform	Identification of patients in need	Identification of care team	Direct referrals from providers	Patient educational resources
Secure messaging center	Easy referral system	Easily develop dual care plans	Manage transitions to dual care	Provider educational resources
Notification of message receipt	Track patient’s service usage/appointment attendance	Communicate with care team via SMS procedures	Decrease time spent on coordinating care	Available community resources and admission criteria
Remote access to system	Link to HIV/PrEP/SU services	Track and manage dual care	Decision trees for referrals	Identify provider availability

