After completion of the 3-session didactic training series, we will enable the mobile application, assign each provider a tablet device, and initiate the 6-month open trial. At this point, the SSL training model will shift from a focus on didactics to ongoing interpersonal support. The SSL relies heavily on supportive interpersonal personal strategies through the use of an external leadership coach and Internal Change Champions, who continually encourage collaborative problem solving throughout the organization. The eight key stakeholders will be responsible for either serving as Internal Change Champions or selecting alternates. The external leadership coach will have monthly coaching calls with the Internal Change Champions focused on tracking implementation progress and engaging in problem solving to address barriers to sustained use of the mobile application. In turn, the Internal Change Champions will be responsible for providing ongoing supervision and support to frontline treatment providers. Consistent with the recommendations of Montague et al. [18], who noted the need for cross-training among HIV and substance use providers, the SSL will include cross-training via explicit didactic instruction and ongoing coaching in an effort to increase understanding of each provider’s role and disease specific processes.

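### Table 3 takes the baseline of a primary outcome, frequency of interagency communication, from an app that is not yet switched on, and this conflicts with the text that points to provider self-report

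*Protocol article*

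**What the plan says.** **Source and status.** In the Measures section, Table 3 has a row for "Frequency/quantity of communication", linked to Hypothesis 2. The entry is MDE at baseline, at 1 and 3 months and at 6 months. The legend defines MDE as "Data extracted through the mobile app dashboard". It explains the star on this row as "Primary Outcome Variable". Hypotheses testing also names frequency of interagency communication as one of two primary variables.

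**Timing.** Table 1 ("Timing of provider enrollment, training, and assessment activities") places baseline provider-level outcomes in the enrolment column, ahead of training at time 0. Training procedures states: "After completion of the 3-session didactic training series, we will enable the mobile application, assign each provider a tablet device". Before that point Table 2 describes only "Hands-on practice with the mobile application using fake patient data".

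**Analysis.** Hypothesis 2 is a comparison with baseline: "HIV providers will report increased frequency and quantity of communication with substance use providers", and the mirror statement for substance use providers. Tests on the primary outcomes "will be conducted using repeated measures ANOVAS on change scores". Effect sizes with 95% confidence intervals are promised for each primary outcome at each follow-up.

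**A different source.** Measures also says that the quantitative measures come from web surveys of leaders and providers at baseline and 1, 3 and 6 months. The verb in Hypothesis 2 likewise implies self-report.

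**The concern.** The study has no control condition, as the Discussion acknowledges, so each provider's baseline is the only comparator. For this outcome the stated source cannot hold any real interagency communication at baseline. A before-and-after contrast would then set an empty record against a live one, and a shift of existing contact into a new channel could not be told apart from more contact.

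The article aims to estimate effect sizes to inform a larger multisite trial. An effect size and interval measured against an empty baseline would carry this artefact into that trial's planning. A pre-training baseline on this source cannot be recovered after the app goes live, so the matter has to be settled before enrolment assessments begin.

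**Working it through.** The article gives no power, alpha or effect size for this outcome, so there is no figure to reproduce. The check is a comparison of passages, followed by an illustration.

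**Step 1: what can the dashboard hold at baseline?**
- Baseline for provider outcomes: enrolment, before training (Table 1).
- App enabled and tablets assigned: after the third session (Training procedures).
- Earlier app use: practice with invented patients only (Table 2).
- Source at baseline: dashboard (Table 3 and legend).

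No real communication can be on the dashboard at baseline, for any of the 60 providers.

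**Step 2: what happens to the contrast?** Let B be the baseline value, A the follow-up app count and D = A − B.
- If B is missing for everyone, D is undefined and the comparison with baseline cannot be made.
- If B = 0 for everyone, D = A, which is never negative. The result can only be no change or an increase.

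**Step 3: how little use would be enough if B = 0?** In an exact two-sided sign test, providers with no app use are ties and drop out. With k users, all differences are positive and p = 2 × 0.5^k.
- k = 5: p = 2 × 0.03125 = 0.0625.
- k = 6: p = 2 × 0.015625 = 0.031.

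Six users suffice at n = 30 or n = 60. If each provider has an assumed 20% chance of any use, the binomial probability of at least six users is 0.57 for n = 30 and 0.99 for n = 60.

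**Step 4: channel shift with no true change.** Assumed inputs, none of them from the article except n: 60 providers; each provider's contact rate drawn from a gamma distribution with shape 1; Poisson counts; total contact constant over time; a share s of contacts moves to the app; baseline scored zero. The test is the time effect in a repeated-measures ANOVA at baseline, 3 and 6 months (the three levels in Hypotheses testing), at an assumed two-sided 0.05. The expected app count per provider is mean × s.

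| Mean contacts | Share moved | Mean app count | Trials rejecting |
|---|---|---|---|
| 4 | 1% | 4 × 0.01 = 0.04 | about 14% |
| 4 | 2% | 4 × 0.02 = 0.08 | about 46% |
| 4 | 5% | 4 × 0.05 = 0.20 | about 99% |
| 4 | 10% or more | 0.40 or more | 100% |
| 1 | 1% | 1 × 0.01 = 0.01 | about 2% |
| 1 | 5% | 1 × 0.05 = 0.05 | about 20% |
| 1 | 10% | 1 × 0.10 = 0.10 | about 63% |

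With the all-channel count at every wave, the same test rejects in about 5%, its nominal level. The rejection rate thus runs from about 2% to 100% according to the contact rate and the share moved.

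**Step 5: is the source stated consistently?** Table 3 says dashboard at all waves. The Measures text says web survey, and Hypothesis 2 says that providers report. These cannot all describe the same row.

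**The case against.** **The table code may simply be wrong.** The survey sentence in Measures and the wording of Hypothesis 2 both favour self-report, so one miscoded row is a live reading. This stands, and it is why the point is put as a contradiction to reconcile and not as a settled choice. It does not remove the problem: Table 3 fixes the source of a primary outcome, and the text on interagency communication mentions only dashboard measurement of app usage. That no survey item on frequency is named is weak evidence by itself, because an article condenses the full protocol.

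**Stronger readings that the article does not support.**
- A reader might infer that any app use at all counts as an increase. That needs the baseline to be scored zero, and the article does not say so. If it is missing, the failure is a different one.
- A reader might infer that Hypothesis 2 as a whole reduces to whether the app was opened. The Levels of Collaboration Scale, also starred for Hypothesis 2, is collected at baseline and at every follow-up.
- A reader might infer that phone, fax and e-mail were the earlier channels and that the dashboard misses them. The audit section names only referrals and consult letters, and Phase 1 is still to establish how information is exchanged. In-app-only counting is a reasonable inference, not a stated fact.
- A reader might infer that a constant baseline breaks the planned ANOVA. This is not shown: the tests are on change scores, with assumption checks and an epsilon correction.

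**It is a pilot.** Feasibility and acceptability are the stated primary objective, and expectations of rejecting null hypotheses are modest. That lowers the stakes of a false positive, but not those of a misleading effect size.

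**Conclusion.** The point holds. As written, this primary outcome has no usable baseline: it is missing, which leaves the planned contrast undefined, or zero for everyone, which lets change go in one direction only. The article also contradicts itself on whether the source is the dashboard or provider report. That much follows from the text and needs no assumption.

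The size of the false signal does rest on assumptions: baseline scored as zero, total contact unchanged, and assumed contact rates and shares moved. Under them the test is close to certain to reject once about 5% of contacts move at a mean of 4, but rejects in only about 20% at a mean of 1. The direction of the bias is firm and its size is illustrative. The damage is confined to this outcome and its effect sizes and intervals.

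**What to change.** - Measure frequency of contact with providers at the other agency across all channels, with the same one or two items in the existing web survey at baseline, 1, 3 and 6 months.
- In Table 3, change the source of this starred row from dashboard to survey, so that it agrees with the Measures text and Hypothesis 2.
- Report dashboard counts from month 1 onward as CCI usage only, with no comparison to baseline.

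**Cost.** One or two items at assessments already scheduled, and an edit to Table 3 and the analysis text. The baseline items must be in place before training starts. The price is recall error and, because the study is uncontrolled and providers know its aim, expectancy bias in self-report. The dashboard counts, shown alongside, give some context for reading the self-reports but do not remove that bias.
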